## **Abstract:**

Globally, depression is the leading cause of disability world worldwide, yet over 75% of people in low and middle-income countries (LMIC) do not receive treatment. This gap is especially large for men. Treating men is essential to reducing the global burden of depression given its impact on families and children with men's mental health (MH) predicting poor parenting and child MH. Although treating parent depression has been shown to improve parental MH, parenting, and child MH; men and fathers have been missing MH care and clinical trials. MH care relevant to fathers that address common barriers to MH, such as masculine norms and economic factors, are needed. This project seeks to conduct a pilot randomized control trial (RCT) using an effectiveness-implementation design in Kenya of a task-shared depression and alcohol use intervention for fathers. The project will build on preliminary work with AMPATH/MTRH that showed proof-of-concept for 'Learn, Act, Engage, Dedicate' (LEAD), a 5-session task-shifted behavioral activation intervention with motivational interviewing and masculinity discussion strategies for fathers in Eldoret that support pursuit of a pilot RCT (n=102 fathers). Specifically, we propose a pilot RCT with fathers randomized to either LEAD or a waitlist control group (with all referred to care as usual at enrollment) to (1) explore change in fathers' MH; (2) explore drivers of change in father MH, father parenting, and child MH (or non-response); and (3) explore the feasibility and acceptability of implementation.

## **Background:**

Depression is the leading cause of disability worldwide, yet over 75% of people in low and middle-income countries (LMICs) do not receive treatment. This gap is especially large for men, who initiate and stay in treatment at rates 4 times lower than women. Improving treatment for men is essential to reducing the global burden of depression given its impact not only on men's wellbeing but also on their families' functioning and children's mental health

(MH). Men's MH impacts child MH both directly and through interparental problems and impaired parenting. Meta-analyses show that treating parental depression improves parenting and child MH. Any comprehensive strategy to reduce the burden of child MH problems (the leading cause of disability among youth) must consider fathers' MH. Despite the impact of fathers' MH on families, fathers are missing from MH treatment. Stigma, masculine norms, and drinking behavior are barriers to men's MH care engagement and retention, worsen men's MH problems, and worsen the consequence men's MH on families and children. Consistent with the Family Stress Model, formative qualitative work we led in Kenya showed a similar pattern: economic pressure and inability to provide were tied to men's depression symptoms, leading to drinking, arguments at home, and poor child MH. Strategies to engage and treat men with depression must address these factors.

To address the lack of relevant services for fathers' depression, I, with a team of Kenyan and US clinicians and researchers, designed and collected preliminary data on LEAD (Learn, Engage, Act, Dedicate), a 5-session behavioral activation (BA) intervention delivered by peer-father counselors that incorporates motivational interviewing (MI) and masculinity discussion strategies. BA, an efficacious intervention for depression, targets depression symptoms by replacing maladaptive behaviors (e.g., isolating, drinking) with valued behaviors. MI, an efficacious treatment for drinking and treatment engagement, is used to engage men in LEAD and address drinking; masculinity discussions expand ideas of what it means to be a father beyond provider only. As a first step, we conducted a proof-of-concept test of LEAD with 9 fathers and 3 peer-father lay counselors in Kenya using a multiple baseline single-case series design. LEAD was acceptable; fathers reported improvements on their depression and drinking, and co-caregivers/partners and children reported improvements in couple's problems, parenting, and child MH. No adverse events were reported.

Here we propose a pilot RCT of LEAD using a Hybrid Type I effectiveness-implementation pilot design that will allow exploration of clinical *and* implementation outcomes simultaneously to inform a future fully powered RCT examining both LEAD effectiveness and implementation sustainability. Guided by the RE-AIM framework— an implementation framework to guide clinical and implementation evaluation, in this pilot

research, we will explore the preliminary effectiveness of LEAD (i.e., change in father MH; potential mechanisms of change in father and child MH) and its implementation (i.e., feasibility and acceptability), randomizing fathers ( $n=102^{28}$ ) with depression (2:1) to LEAD delivered by peer-father counselors or to waitlist control (offering LEAD after final assessment). All groups will be referred to care as usual at enrollment. I will explore clinical change between groups to inform a future definitive RCT recognizing that we are not powered to estimate definitive effectiveness of LEAD here.

### Specific Aims

**Aim 1. Explore the preliminary effectiveness of LEAD on father MH.** The *primary outcome* is father depressive symptoms assessed by the Patient Health Questionnaire, previously validated in Kenya. *Secondary outcomes* include fathers' drinking, father parenting, interparental problems, and child MH (ages 8-17) reported by the father, co-caregiver, and one child immediately and 1-month and 3-months post-LEAD.

**Aim 2. Use mixed methods to explore mechanisms driving change in father MH, father parenting, and child MH.** I will use structural equation modeling to explore clinical mediators between LEAD and father and child MH: LEAD → positive activities → father MH → parenting → child MH. To explore patterns of response/non-response, I will conduct qualitative interviews (fathers, co-caregivers, children, peer-counselors) on perceived change pathways and analyze LEAD-session transcripts of families showing different change outcomes (e.g., all changed, none, father MH only, child MH only). Qualitative data will be analyzed using the Framework Method. Data will be integrated to generate hypotheses and refinements.

**Aim 3. Explore feasibility and acceptability of implementing task-shifted MH treatment for fathers.** A mixed-methods process evaluation with fathers, peer-fathers, and delivery stakeholders will explore *implementation outcomes*: reach; retention; fidelity; feasibility; acceptability; and barriers to/facilitators of implementation, scale-up, and sustainability, including questions related to social determinants of health, e.g., gender norms, poverty, (interviews, focus groups, surveys).

## Methods:

### Study design:

This will be a pilot RCT using a hybrid type 1 implementation. Results will be evaluated using mixed methods (qualitative and quantitative methods).

### Study setting:

Research will be conducted in Eldoret, the fifth most populated city in Kenya, in collaboration with MTRH and AMPATH. AMPATH administers clinic- and community-based programs for medical care and broader programs focused on poverty reduction and child wellness. MTRH has Departments of Psychiatry and Psychological Counseling and an inpatient rehabilitation center. AMPATH supports numerous research programs and services. Participants and peer providers will be recruited from the community (Eldoret and surrounding areas) as described below.

### Recruitment & Inclusion Exclusion Criteria:

We will work with **community leaders, peer-leaders supporting community substance use groups, and** existing Community Health Workers (CHWs) to recruit and identify eligible fathers with depression, any drinking, and a child at risk for MH problems (n=102 **Table 1**), one target child for each father and a co-caregiver (partner or relative who can report on family and child). *We will recruit to achieve balance in child age (50% 8-12, 50% 13-17).* All eligibility cut-off scores are based on validated measures. Inclusion includes the following: (1) Male between the ages of 18-65; (2) live with and be responsible for at least one child between the ages of 8 and 17 years of age; (3) screen positive for depression symptoms, operationalized as a score above 5 on the patient health questionnaire (PHQ-9); (4) Any reported alcohol use in the past 45 days measures with the AUDIT (score 1 or above); (5) child at risk of mental health issues as indicated by a score above 13 on the Strengths and Difficulties Questionnaire (SDQ) reported on by any caregiver; (6) willingness for co-caregiver and target child to participate in assessments (previously piloted strategy). Exclusion criteria includes: (1) Severe depression symptoms indicated a score above 19 on the PHQ-9; (2) Severe risk/likely alcohol dependence that warrants medical management indicated as a score 20 or above on the alcohol use disorder identification test (AUDIT); (3) Severe risk/likely substance use dependence that

warrants medical management indicated as a ‘yes’ response in two or more questions in CAGE-AID; CAGE-AID is a standardized tool which is an adaption of the CAGE used for conjointly screening alcohol and drug dependence (Maina, Elizabeth & Wagoro, Miriam & Angeline, Kirui & Lincoln, Khasakhala.,2017). The CAGE-AID, as a screener, has shown validity as a screening tool for both alcohol dependence and drug dependence (Brown, R. L., & Rounds, L. A.,1995). The screener was originally adapted from the CAGE a standardized tool for measuring alcohol dependence whose acronym stands for ‘Cut down, Annoyed, Guilty, Eye opener’ (4) violent legal offenses (one question); (5) Indicators of severe violence at home assessed with key items from the Conflict Tactics Scale (CTS); (6) Inability to provide informed consent of complete procedures in Swahili or English; (7) serious mental illness (current or history); We use a low depression threshold for inclusion, given men often underreport symptoms; at this piloting stage, we will try to recruit men who have a child at risk for MH problems to explore how father treatment may influence child MH change (Aim 2). The youth does not have to be father’s biological child, just responsible for the care of the child and involved in the child’s life. The SDQ has shown sensitivity to change in Kenya.

**We will work with the on-site PI, study staff, and the MTRH community-based substance use group lead to identify community and peer leaders including CHWs. [Community leaders can consist of chiefs, village elders, religious leaders, or individuals well-connected in communities; individuals with formal and informal community positions, longstanding community knowledge, and can represent diverse sectors of the community. Peer-leaders are individuals with lived-experience who lead community-based substance use groups within Eldoret and surrounding communities.] We will approach leaders about the study to assess their interest in helping recruit fathers and peer-father counselors. If so, we will describe the type of fathers we hope to recruit using lay-terms based on inclusion and exclusion criteria. Leaders will then work with the trained consenters, Kenyan RA(s) and/or the PC who are all Kenyan psychologists, to reach out to potential participants, assess interest, and conduct eligibility screening and consent and assent procedures. Consenters will be trained to provide**

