**Version 4. Clean Date: September 18,2024**

| Table 1. Father Recruitment Criteria                                                                                            |   |
|---------------------------------------------------------------------------------------------------------------------------------|---|
| Inclusion Criteria                                                                                                              |   |
| Live with and be responsible for the care of at least one child aged 8-17 years                                                 |   |
| 18 to 65 years of age                                                                                                           |   |
| Elevated depression symptoms (PHQ-9 > 5)                                                                           |   |
| Any alcohol use (AUDIT>0)                                                                                                       |   |
| Child at risk of MH problems (SDQ > 13)                                                                            |   |
| Willingness for family member to participate                                                                                    |   |
| Exclusion Criteria                                                                                                              |   |
| Severe depression symptoms (PHQ-9 > 19)                                                                                         |   |
| Severe risk/likely alcohol dependence that warrants medical management (AUDIT > 20)                                |   |
| Severe risk/likely substance use dependence that warrants medical management (‘yes’ score in two or more questions in CAGE-AID) |   |
| Violent legal offences                                                                                                          | 2 |
| Any indicator of severe violence (CTS items)                                                                                    |   |
| Inability to provide informed consent, and/or complete procedures in Swahili or English (orally).                               |   |

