referrals to care in the area to all individuals who report problems or referrals to higher levels of care to those who need it. Referral will continue to include the community substance use groups run by MTRH when appropriate. Consenters will complete the consent process and conduct the eligibility screening first with the father and then with other family members when the father is eligible. Eligibility and screening will occur first with fathers, then co-caregivers, then the target child. The target child will be chosen based on age first, then highest SDQ score based on caregiver screeners. *All individuals who report symptoms will be referred to care as usual.*

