**Consenting and Safety Considerations:** The study will follow WHO guidelines on conducting research with individuals who may be at risk of violence as a precaution. Guidelines will inform consent forms, procedures, and personnel training. Procedures are detailed in Human Subjects 3.1. Briefly, with fathers, **trained consenters** (i.e., the study RA and PC and or other trained medical psychologists) will assess interest, complete consent, and conduct eligibility screening. Study inclusion/exclusion will be explained in general terms to not place any youth or co-caregivers at risk later if a family is ineligible. Scripts will be developed with our community partners. Fathers excluded due to severe symptomology or severe violence will be referred to a higher level of care within MTRH (Human Subjects 3.1). The CHW will ask eligible fathers for permission to invite a co-caregiver to answer screening questions about the child, emphasizing that all information beyond basic study detail will be kept private from the co-caregiver and vice versa (a process used in the proof-of-concept pilot). The co-caregiver will then be consented and screened in a private location (SDQ; CTS); if the CTS indicates presence or likelihood of severe violence, a safety assessment will be conducted and referrals provided while respecting women's autonomy. Fathers' ineligible in this scenario will be revisited later by the CHW, asked dummy questions, and told they are ineligible using non-descript language; referrals and an appointment to care will be provided to MTRH. If the father is eligible after both screenings, the target child will complete assent and a brief screen (SDQ). **Recruitment feasibility:** Based on ongoing studies, we estimate recruiting 2-4 fathers per week. This rate will allow us to recruit 102 families within 24 months.

**Peer-father counselor recruitment, training, supervision.** To recruit, select, supervise, and train peer-father counselors, we will use approaches employed in our preliminary pilot that

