## Treatment Conditions

**Intervention.** LEAD comprises behavioral activation (BA) and motivational interviewing (MI), as well as discussions of masculinity and a family focus throughout to target father's depression symptoms and

common comorbidities, such as drinking. LEAD is guided by a manual (in Swahili and English). It includes five, 60-90-minute weekly sessions. LEAD was adapted for context based on formative work. Each session begins with MH assessment and review of activity completion and ends with homework to monitor

activities. **Brief BA** has shown efficacy reducing depression symptoms as well as co-morbid alcohol and substance use across contexts and when delivered by lay-counselors. LEAD uses core BA components. **MI** (Session 1) has shown efficacy for increasing MH treatment engagement and reducing drinking behaviors, with strong effects when delivered by lay counselors. LEAD uses MI strategies to engage men in the treatment and increase commitment to addressing problems. MI strategies are then integrated throughout BA (Session 1-5) to enhance father motivation to complete activities as well as to build self-efficacy (e.g., when reviewing homework, counselors reflect successes).

**Waitlist Control (WL).** Those randomized to WL will complete assessments and be monitored at each timepoint; they will be offered LEAD following the last assessment. In a pilot, a control allows for a realistic examination of recruitment, randomization, implementation of LEAD, assessment procedures, and retention. If safety concerns arise, referrals and safety procedures will be implemented.

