## Data Collection and Sampling and Power

We will compare LEAD to a monitored waitlist control (WL) on preliminary clinical and implementation outcomes. Using a random number generator in RStudio, we will randomize participants 2:1 to LEAD:WL, stratified by levels of drinking to ensure group exchangeability. Assessments will occur at baseline, immediately following LEAD, 1-month, and 3-month post-intervention. WL participants will be assessed at each timepoint; after the last assessment (~4.5 months), they will be offered LEAD.

Each father and his co-caregiver and designated child will complete assessments on family problems and MH at each timepoint (both arms); a procedure previously piloted. For fathers in LEAD, proximal mechanism outcomes will be assessed during LEAD (e.g., activity completion; Table 2). A subset of fathers, co-caregivers, and children in the LEAD arm will complete qualitative interviews 1 month after LEAD; peer-father counselors (N=12) and delivery stakeholders (supervisors, community leaders, MTRH personnel) will complete focus group

discussions and  
brief surveys 1-  
month post-LEAD.  
Trained Kenyan RAs  
will conduct  
assessments in

| Table 2. Aim 1 and Aim 2 Quantitative Measures |                                     |                                         |          |     |                     |
|------------------------------------------------|-------------------------------------|-----------------------------------------|----------|-----|---------------------|
| Outcome                                        | Construct                           | Measures*                               | Reporter | Aim | Alpha in Kenya      |
| Primary                                        | Depression Symptoms                 | PHQ-9                      | F        | 1   | .91                 |
| Secondary                                      | Drinking; Gender Norms              | AUDIT  ; GEM  | F        | 1   | .89; .56            |
|                                                | Disrupted Parenting +    | APQ                     | F, Co, C | 1   | F=.78, P=.85, C=.92 |
|                                                | Interparental Problems + | Togetherness Scale         | F, Co, C | 1   | F=.95, P=.96, C=.95 |

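### The text excludes AUDIT scores of 20 or above but Table 1 excludes only scores above 20, so a father scoring exactly 20 is excluded by one rule and passes the AUDIT criterion under the other

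*Protocol*

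**What the plan says.** The Recruitment & Inclusion Exclusion Criteria section of the protocol lists, as its second exclusion, alcohol dependence judged likely enough to need medical management, "indicated as a score 20 or above on the alcohol use disorder identification test (AUDIT"). Table 1 (Father Recruitment Criteria) in the same section repeats the criterion as "Severe risk/likely alcohol dependence that warrants medical management (AUDIT > 20").

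The AUDIT inclusion rule also appears in both places. The text has any alcohol use "measures with the AUDIT (score 1 or above"), and Table 1 has "Any alcohol use (AUDIT>0").

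Three other passages bear on what happens to a father at the boundary:

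- The paragraph following Table 1 has consenters give "referrals to higher levels of care to those who need it".
- Consenting and Safety Considerations states: "Fathers excluded due to severe symptomology or severe violence will be referred to a higher level of care within MTRH".
- Data Collection and Sampling and Power states that "we will randomize participants 2:1 to LEAD:WL", and that waitlist fathers are offered LEAD after the last assessment, at about 4.5 months.

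**The concern.** Both statements are current protocol text, and the recruitment text itself points the reader to Table 1. They put the boundary on different sides of 20. Several trained consenters do the screening, so two of them, each following the protocol, could reach opposite decisions on the same man. A monitor could not then say whether enrolling him was a deviation.

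The criterion exists to keep men who probably need medical care for alcohol out of a five-session lay-counsellor programme and its waitlist. Reading it one way or the other therefore decides whether a father at 20 is excluded and referred upward, or can be randomised.

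**Working it through.** **Inputs.** The two exclusion cut-offs (text: 20 or above; Table 1: > 20) and the two inclusion cut-offs (text: 1 or above; Table 1: > 0). AUDIT totals are taken to be whole numbers.

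**Scores admitted on the AUDIT criterion.**

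- Text: s ≥ 1 and not s ≥ 20, which gives 1 to 19, or 19 scores.
- Table 1: s > 0 and not s > 20, which gives 1 to 20, or 20 scores.
- Difference: 20 − 19 = 1 score, namely s = 20. Every other score is classified the same way.

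**Is Table 1 simply loose with its signs?** Eight numeric cut-offs stand in both places:

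| Rule | Text | Table 1 | Same cut-off? |
|---|---|---|---|
| Father's age | 18–65 | 18–65 | Yes |
| Child's age | 8–17 | 8–17 | Yes |
| PHQ-9 inclusion | above 5 | > 5 | Yes |
| AUDIT inclusion | 1 or above | > 0 | Yes, on whole numbers |
| SDQ inclusion | above 13 | > 13 | Yes |
| PHQ-9 exclusion | above 19 | > 19 | Yes |
| AUDIT exclusion | 20 or above | > 20 | **No, differs at 20** |
| CAGE-AID exclusion | two or more yes | two or more yes | Yes |

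Seven of eight agree. The text separates a strict bound (above) from an inclusive one (or above), and Table 1 keeps that distinction elsewhere: the inclusive AUDIT bound of 1 becomes > 0. By the same conversion the inclusive bound of 20 should become > 19 or ≥ 20.

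**Consequence for a father at exactly 20 who meets all other criteria.**

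- Text: excluded and referred to a higher level of care at MTRH.
- Table 1: can be randomised 2:1, so the chance of waitlist is 1 / (2 + 1) = 1/3, with LEAD offered at about 4.5 months.

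**After correction.** With Table 1 at ≥ 20, both sources admit 1 to 19 and no score is classified differently.

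**The case against.** The strongest doubt concerns a single character. A ≥ sign or an underlined > in a table cell can be lost when a PDF is converted to text, and Table 1 shows other signs of damage, such as a stray digit in the row on violent offences. The ≥ sign does survive under Data Management and Analysis, where retention is defined, but that is running prose and says little about a table cell. The possibility stands but is unproven, and a look at the original page would settle it.

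Second, Table 1 is an abbreviated summary. It omits, for example, the 45-day window for alcohol use and the serious-mental-illness exclusion. Since any one exclusion suffices, one could hold that the text removes a father at 20 whatever the table says. That is a sensible reading, but the protocol does not state it. A summary that leaves a criterion out is also different from one that gives a conflicting number for it.

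Third, the harm is cushioned. Referral upward depends on need and not only on exclusion. For waitlist fathers, "If safety concerns arise, referrals and safety procedures will be implemented". The Risks section also lets staff refer participants to specialist care. This stands: a waitlisted father at 20 would not necessarily go without referral for 4.5 months. It reduces the consequence without resolving which rule applies.

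**Conclusion.** The contradiction is real on the protocol as it reads, and it should be fixed. It affects one whole-number score. A father at 20 is excluded by the text; under Table 1 he passes the AUDIT criterion and would still have to meet every other one. The protocol gives no AUDIT distribution, so the number of fathers affected is unknown and probably small. Sample size, power and analysis are untouched. The point deserves correction because the cut-off is a safety threshold, not a descriptive one, and must give one answer. The conclusion assumes whole-number AUDIT totals and that the printed sign in Table 1 is >.

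**What to change.** Change the AUDIT exclusion in Table 1 to ≥ 20, to match the text. This is also the more cautious of the two rules. Confirm that the screening form or tablet logic uses the same cut-off. If screening has begun, look up any father who scored exactly 20, record how he was handled, and make sure that any such father who was enrolled has been offered referral to a higher level of care. The cost is a one-character correction and a short check of the screening records, with no change to sample size, schedule or analysis.
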